##### Watch videos about prostate cancer.

2.5.3.2.

Participants can select from various short video testimonials (1–10 min) from four AA prostate cancer survivors living in Oklahoma. These videos are narrative-focused and convey powerful, personal stories about key topics of a prostate cancer journey for AA men (see Table 3) [43].

##### Talk with a prostate cancer survivor.

2.5.3.3.

The survivors who tell their stories in the videos also provide social support to participants in the study as “peer coaches.” [44] Participants can request a conversation with one of the four survivors and also select from a list of topics to prioritize (see Table 3). The study team schedules these conversations, and survivors use a study phone.

Similar to the Taskforce App, the Genius App also includes the following On-Demand features: (1) Order a Home-Based PSA Test Kit, (2) Report My PSA Test Results, (3) Track My Rewards, and (4) Report a Problem.

#### Scheduled assessments

2.5.4.

Both study apps use on-demand features and scheduled assessments to promote engagement with app features. For example, the Genius App has a scheduled assessment on Day 2 of study participation (“Prostate Cancer Survivor Introduction”) to deliver a video introducing the names and backgrounds of the participating prostate cancer survivors. However, participants can complete an on-demand feature (“Talk With a Prostate Cancer Survivor”) at any time during the study to schedule a phone conversation with one of the four prostate cancer survivors (see Table 4 for an overview of scheduled assessments).

### Theoretical framework

2.6.

Each unique app feature and assessment within the Genius App is posited to affect a proximal outcome, such as prostate cancer knowledge, which in turn is believed to act as a mechanism through which the app feature will increase the completion of PSA screening (see Fig. 1 for conceptual diagram). For example, the Health Belief Model (HBM) posits that knowledge about a disease is an antecedent to motivated information processing. Thus, we have included culturally tailored interactive learning modules and testimonial videos to improve knowledge about prostate cancer, risk factors, screening, etc. Similarly, the HBM posits that people will engage in a health behavior when they acknowledge the high perceived severity of a health threat, their high susceptibility to that threat, and the benefits of the health behavior to remove the threat (i.e., PSA screening). The survivor testimonial videos were filmed and construct-mapped to address these pathways. The HBM highlights the need to partner interventions that address both perceived and structural barriers to engaging in health behavior. Thus, we provide access to on-demand screening through a free at-home PSA test [45,46] and employ the Extended Parallel Process Model (EPPM) to construct risk and efficacy messaging through the tailored barrier reduction messages [47,48]. Social support is considered a third protective mechanism when coping with health threats [49–51]. Social support can directly promote better management of health threats and increase engagement with health behavior change. Social support buffers individuals against emotional burden when preparing to change or complete a health behavior, so we incorporated a feature that allows participants to contact and have conversations with prostate cancer survivors [49–51].

### At-home PSA test kits

2.7.

The study team partnered with imaware^™^ (https://www.imaware.health/) to deliver study-provided at-home PSA test kits to men who ordered one during the study. The at-home PSA test collects a small sample of blood using the finger prick, which correlates strongly with PSA levels in venous blood, and CLIA-certified, CAP-accredited labs analyze these kits, the gold standard in lab testing quality regulation [52–54]. Each kit has detailed instructions for how to do the finger prick correctly, and a video link will be provided to participants who need additional instructions. Participants can also request help from study staff to provide support on how to complete the test over the phone. Participants will mail their test kits to imaware^™^, and the company will analyze the blood sample. Once imaware^™^ analyzes the sample, the PSA results will be shared with the participant through a portal login (see Fig. 3 in Supplemental Materials).

### Study surveys

2.8.

#### Screening survey

2.8.1.

Participants will complete a REDCap screening survey when they click an advertisement for the study. The screener consists of 37 items that assess demographics, English literacy, prostate cancer and screening history, and other eligibility criteria. See Table 5 for a list of variable categories across assessment types.

#### Enrollment assessment

2.8.2.

Participants who are found to be eligible for the screener will be contacted by phone and will complete the final screening items. Specifically, participants will e-sign study documents, including informed consent, a HIPAA form to enable contact with imaware^™^, and an agreement to take care of and return the study phone. Participants will be asked about their preferred assessment time for weekly smartphone-based assessments. In addition, participants’ literacy will be assessed using the seven-item Rapid Estimate of Adult Literacy in Medicine – Short Form [37].

#### Baseline survey

2.8.3.

Participants will complete the REDCap baseline survey before being randomly assigned to a study condition. The baseline survey consists of a total of 365 items that assess sociodemographic characteristics (e.g., education, insurance status), social determinants of health (e.g., food and financial security), physical (e.g., Behavioral Risk Factor Surveillance System health conditions) and psychological wellbeing (e.g., GAD-7, PHQ-9), health behaviors (e.g., smoking, sleep), patient-provider relationship (e.g., medical mistrust), general cancer screening history and attitudes (e.g., screening self-efficacy, perceived threat), as well as prostate cancer-specific knowledge and attitudes (e.g., decisional conflict scale).

#### Weekly smartphone-based surveys

2.8.4.

Using the INSIGHT^™^ mHealth Platform, participants in both study conditions will be prompted during their preferred assessment time by their smartphones to complete weekly surveys for four weeks (on days 7, 14, 21, and 28 post-randomization). The phone will audibly and visually cue these surveys for 30 s. The assessment will be recorded as missed if a participant does not respond after five prompts. All assessments will be date- and time-stamped for future analyses. Weekly surveys assess the frequency of app use, satisfaction with assigned app content, knowledge and perceptions of prostate cancer screening, readiness to complete a PSA test, and current emotional states.

#### Post-intervention survey

2.8.5.

Participants will gain access to a post-intervention survey 30 days after they are randomized to a study group. The post-intervention survey assesses prostate cancer health and screening beliefs, attitudes, behaviors, and acceptability with the smartphone app (e.g., user engagement scale, system usability scale).

#### Exit interview

2.8.6.

All participants will complete the qualitative exit interview that measures their overall attitudes toward the study and the prostate cancer screening process. Participants assigned to use the Genius App will be asked about their experience completing learning modules, their thoughts about survivor videos, and their conversations with survivors. All participants will be asked about the efficacy of using the app to order an at-home PSA test kit and attitudinal changes in prostate cancer screening after using their respective app. See Table 6 for qualitative domains asked by study condition.

### Study compensation

2.9.

All participants who enroll in the study will receive a Greenphire Mastercard [55,56] to facilitate payment for completing study surveys. Participants earn $25 for completing the enrollment survey, $50 for completing the baseline survey, $50 for completing the post-intervention survey, $50 for completing their exit interview, and $25 for returning their study materials after completing all study activities. Participants can earn an extra $25 for completing their baseline and post-intervention survey within 72 h of being granted access to them. Participants can earn $20 for each weekly survey they complete on their smartphones (up to $80 in total compensation). Participants can earn up to $330 on their Greenphire Mastercard if they complete all study activities.

### Outcome measures

2.10.

#### Primary outcome

2.10.1.

The primary outcome measure is prostate cancer knowledge, assessed using the Prostate Cancer Knowledge Scale [57] administered at baseline and post-intervention surveys. The scale consists of 18 items that assess screening (6 items), risk factors (5 items), and warning signs (7 items) of prostate cancer. This scale has strong internal consistency (α = 0.80) and has been validated for AA adults. [57]

#### Secondary outcomes

2.10.2.

Imaware^™^ will share information about PSA results with our research team to allow for the calculation of test completion rates. Participants have 30 days to order a PSA test kit. Perceptions of how engaging the app will be measured during the post-intervention assessment using the User Engagement Scale (UES) [58], which is a 31-item multidimensional scale measuring six distinct dimensions of (a) aesthetic appeal, (b) focused attention, (c) novelty, (d) perceived usability, (e) felt involvement and (f) endurability. The System Usability Scale (SUS) [59] will measure *perceived accessibility*, a 10-item bidimensional scale of (a) how useable and (b) how learnable the app was.

### Power analysis

2.11.

We anticipate that 20 % of the full sample will be lost to attrition; therefore, the sample size power calculation is based on 60 participants. Assuming the mean (standard deviation) of baseline knowledge in the Taskforce App is 11.1 (3.1) [60] and a two-sided alpha of 0.05, we will have 80 % power with *N* = 60 (30/group) to detect a difference of 2.3 points on Prostate Cancer Knowledge Scale.

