## Method

2.

AA men (*N* = 80), aged between 55 and 69, and who are not up to date with PSA screening according to recommended United States Preventive Services Taskforce (USPSTF) guidelines [17], will be randomly assigned 1:1 to one of two study conditions: the Taskforce App (control condition) or the Genius App (intervention condition). The Taskforce App [34] condition includes an educational app previously developed by USPSTF and the U.S. Department of Health & Human Services, a study app that includes study assessments, and a button to order an at-home PSA test. All participants will receive a study-provided, pre-paid smartphone (Samsung Galaxy S21). Both conditions will complete a baseline survey, use their respective smartphone app for 30 days, complete four once-weekly smartphone surveys, complete a one-month post-intervention survey, and be asked to complete a semi-structured exit interview after their post-intervention survey. The Genius App (see Fig. 1 in Supplemental Materials for app comparisons) will use responses to weekly smartphone surveys to guide tailored navigation content for the at-home PSA test. The study launched in February 2023 during Black History Month and is currently enrolling participants. The University of Oklahoma Health Sciences Center (reference number: 14666) institutional review board approved the protocol presented in this study. This trial was registered at ClinicalTrials.gov (NCT05331638).

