### Analytical plan

2.12.

We will assess pre-post intervention group differences on the Prostate Cancer Knowledge Scale using a two-sample *t*-test. Linear regression will also be used to estimate the post-intervention difference on the Prostate Cancer Knowledge Scale while accounting for the participant’s baseline score on the Prostate Cancer Knowledge Scale and demographic and psychosocial characteristics (e.g., age, insurance status). We anticipate that the participant characteristics, family history of prostate cancer, and literacy level will be well balanced by randomization. However, we will examine the potential moderating effect of these variables on pre-post group differences in the Prostate Cancer Knowledge Scale.

PSA screening test rates will be calculated for (1) the overall screening rate across both groups and (2) Taskforce App vs. Genius App. A chi-square test of independence (or Fisher’s exact test, as appropriate) will be used to compare PSA screening test completion rates between study conditions. We will also examine between-group differences (Taskforce App vs. Genius App) at follow-up through the overall score of UES and each of the six dimensions using two-sample *t*-tests. For perceived accessibility, we will also use two-sample t-tests to explore between-group differences, as measured via the overall score of SUS.

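### The stated 80% power fits a t-test on a single knowledge score, but the analysis section words the test as one on pre-post differences; on change scores, 80% needs a pre-post correlation of at least about 0.49

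*Protocol article*

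**What the plan says.** Section 2.11 (Power analysis) of the protocol article gives these inputs:

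- Mean and SD: "Assuming the mean (standard deviation) of baseline knowledge in the Taskforce App is 11.1 (3.1").
- Error rate: "a two-sided alpha of 0.05".
- Power and analysed sample: "we will have 80 % power with *N* = 60 (30/group").
- Target: "to detect a difference of 2.3 points on Prostate Cancer Knowledge Scale".

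It gives no SD of change and no correlation between the baseline and post-intervention scores.

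Section 2.12 (Analytical plan) names the test for the primary outcome: "We will assess pre-post intervention group differences on the Prostate Cancer Knowledge Scale using a two-sample *t*-test". The same section also plans a linear regression of the post-intervention score that adjusts for the baseline score and for participant characteristics.

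Two other places describe the primary comparison differently. The results paragraph of the abstract speaks of group differences after the intervention. The primary hypothesis in the Discussion is that the Genius App arm will have greater knowledge after the intervention. Neither mentions change from baseline.

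**The concern.** A two-sample t-test needs one number per man. If the comparison concerns a pre-post difference, that number is his change score, and the relevant SD is that of the change. The power section instead uses the SD of one baseline measurement. The two SDs coincide only at a particular correlation, which the article does not state.

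The wording of section 2.12 favours the change-score reading. It describes the User Engagement Scale comparison as one at follow-up and the regression as estimating a post-intervention difference, but uses pre-post wording for the knowledge t-test and again for the moderator analysis. The authors had words for a follow-up-only comparison and did not use them for this test.

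At stake is how a null result would be read. The Discussion says that a successful pilot will support a statewide effectiveness trial. If the true power for 2.3 points were about two in three rather than four in five, a non-significant result would be weaker evidence against the app than readers are led to believe.

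**Working it through.** **Inputs** (section 2.11): SD = 3.1, n = 30 per arm, difference = 2.3, two-sided alpha = 0.05. The pre-post correlation rho is not in the article, so a range is shown. Assumption: SD 3.1 at both time points and in both arms.

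**1. Reproduce the stated figure with one score per man.** The standardised difference is 2.3 / 3.1 = 0.742. The noncentrality is 0.742 × sqrt(30/2) = 2.87 on 58 degrees of freedom.

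- Power from the noncentral t: 80.7% (normal approximation: 82.0%).
- Detectable difference at 80% power: 2.28 points, which the article rounds to 2.3.

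The figure reproduces.

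**2. Change-score t-test.** With equal SDs, SD of change = 3.1 × sqrt(2 × (1 − rho)). This equals 3.1 when rho = 0.5.

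**3. Baseline-adjusted regression of the post score.** The residual SD is about 3.1 × sqrt(1 − rho²), which never exceeds 3.1. The detectable difference is 2.28 × sqrt(1 − rho²). The calculation ignores the few degrees of freedom spent on covariates.

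| rho | SD of change | Power, change score | Detectable difference, change score | Power, baseline-adjusted | Detectable difference, baseline-adjusted |
|---|---|---|---|---|---|
| 0.2 | 3.92 | 60.8% | 2.88 | 82.2% | 2.23 |
| 0.3 | 3.67 | 66.6% | 2.70 | 84.2% | 2.18 |
| 0.4 | 3.40 | 73.2% | 2.50 | 86.9% | 2.09 |
| 0.5 | 3.10 | 80.7% | 2.28 | 90.4% | 1.97 |
| 0.6 | 2.77 | 88.5% | 2.04 | 94.2% | 1.82 |
| 0.7 | 2.40 | 95.4% | 1.77 | 97.7% | 1.63 |

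Powers are for 2.3 points at 30 per arm; detectable differences are at 80% power.

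**4. Break-even correlation for the change-score test.** Exactly 80% power for 2.3 points at 30 per arm needs an SD of change of 3.127. Then rho = 1 − (3.127 / 3.1)² / 2 = 0.49.

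**5. The three readings side by side.**

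- t-test on post-intervention scores: 80.7% whatever rho is, provided the post-intervention SD is 3.1.
- Baseline-adjusted regression: about 80.7% at rho = 0, and more as rho moves away from zero.
- t-test on change scores: below 80% when rho is under about 0.49, above it otherwise.

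**The case against.** The strongest reply is that the calculation is sound for the comparison in the abstract and the primary hypothesis. For a post-intervention comparison, a cross-sectional SD is the right kind of input and the 80% reproduces at any correlation. This stands, and it means that the change-score reading, though the natural one for section 2.12, is not settled. It does not make the text consistent: if the abstract and Discussion govern, section 2.12 misdescribes the test; if section 2.12 governs, section 2.11 powers a different one.

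A second reply is that the printed numbers also fit an unstated correlation of 0.5, at which the SD of change is exactly 3.1. A condensed article may simply not report it. That is possible. What can be shown is that the article does not state the basis, not that the calculation was done wrongly.

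Third, the plan has some slack. The article says: "We anticipate that 20 % of the full sample will be lost to attrition; therefore, the sample size power calculation is based on 60 participants". But 20% of 80 is 16, which leaves 64, or 32 per arm. At 32 per arm the break-even correlation falls to about 0.46 and change-score power at rho = 0.4 rises to 76%. At rho = 0.3 it is still only about 70%, so the slack narrows the gap without closing it. The pilot purpose likewise lowers the stakes, but the article chose to make a power claim.

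A reader might go further and infer that the trial is underpowered, or that 80% holds only at a correlation close to 0.5. Neither follows. Nothing in the article indicates that rho is below 0.5, and above about 0.49 the change-score test has more power than stated.

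**Conclusion.** The point holds as a mismatch between the basis of the power calculation and the wording of the planned test. The arithmetic in section 2.11 is correct for a single score with SD 3.1. Of the three analyses that the article's wording allows, only the change-score t-test can fall materially short of 80%, and only for correlations below about 0.49. At 0.3, the chance of missing a true 2.3-point difference would be about one in three (100% − 66.6%) instead of the one in five stated.

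These sizes rest on equal SDs of 3.1 at both times and in both arms, 30 analysed per arm, and a correlation that has to be assumed. Confidence is moderate, because the article does not settle which comparison is primary. The correction should be made because it fixes what the primary analysis is and what the power claim refers to.

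**What to change.** - **Name one primary comparison** and use it consistently in the abstract, section 2.12 and the Discussion. The baseline-adjusted regression of the post-intervention score is preferable: it is already planned, the baseline score is collected before randomisation in both arms, and under the stated SD its power is about 80% or more at every correlation.
- **If that regression is primary,** say in section 2.11 that 80% power for 2.3 points at 30 per arm is a conservative bound corresponding to zero correlation. Add that the detectable difference is about 2.2 to 1.6 points for correlations of 0.3 to 0.7, assuming SD 3.1 at both times.
- **If the change-score t-test stays primary,** state the assumed correlation or SD of change, with its source, and the power that results.
- **If the t-test on post-intervention scores is meant,** reword section 2.12 accordingly and state that the SD of 3.1 is assumed to apply after the intervention.

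The cost is rewording a few sentences and designating the primary analysis. No additional participants or data are needed.

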### Analytical plan

2.12.

We will assess pre-post intervention group differences on the Prostate Cancer Knowledge Scale using a two-sample *t*-test. Linear regression will also be used to estimate the post-intervention difference on the Prostate Cancer Knowledge Scale while accounting for the participant’s baseline score on the Prostate Cancer Knowledge Scale and demographic and psychosocial characteristics (e.g., age, insurance status). We anticipate that the participant characteristics, family history of prostate cancer, and literacy level will be well balanced by randomization. However, we will examine the potential moderating effect of these variables on pre-post group differences in the Prostate Cancer Knowledge Scale.

PSA screening test rates will be calculated for (1) the overall screening rate across both groups and (2) Taskforce App vs. Genius App. A chi-square test of independence (or Fisher’s exact test, as appropriate) will be used to compare PSA screening test completion rates between study conditions. We will also examine between-group differences (Taskforce App vs. Genius App) at follow-up through the overall score of UES and each of the six dimensions using two-sample *t*-tests. For perceived accessibility, we will also use two-sample t-tests to explore between-group differences, as measured via the overall score of SUS.

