**Results::**

We will evaluate the preliminary efficacy of the apps via post-intervention group differences on the validated 18-item Prostate Cancer Knowledge Scale (primary outcome). We will also explore post-intervention group differences in perceived engagement, accessibility, and acceptability between the apps. Finally, we will derive preliminary estimates of PSA screening rates between study conditions and identify mechanisms of screening adherence.

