## Discussion

4.

Prostate cancer is the most diagnosed cancer in AA men and the second‑leading cause of cancer-related deaths [64–66]. The current pilot study will test the first-of-its-kind mHealth app to improve prostate cancer knowledge and increase PSA screening uptake among AA men using home-based screening methods. The Genius App is theory-driven and community-guided, offering culturally tailored education about prostate cancer for AA men. Our primary hypothesis is that participants randomly assigned to the Genius App will report significantly greater knowledge on the Prostate Cancer Knowledge Scale post-intervention than participants randomly assigned to the Taskforce App. We will also derive preliminary estimates of the effects of each prostate cancer screening app on at-home PSA screening test completion rates.

This study has many notable strengths. First, it focuses on a high-risk group with a limited history of prostate cancer screening, concentrating on an important public health disparity [64]. Second, it addresses many of the methodological limitations of existing prostate cancer screening app pilot studies through a rigorous experimental design [24,67]. Third, via weekly smartphone assessments, the study will measure mechanisms of behavior change, including the cognitive and emotional changes that individuals go through when engaging with a longitudinal cancer screening intervention that is otherwise not collected in standard screening interventions. Fourth, the remotely delivered, culturally responsive intervention addresses both patient-level factors (i.e., equitable access to screening) and structural-level factors (i.e., equitable access to culturally tailored information for AA men) that disproportionately affect AA men [68–71].

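### No analysis of the primary outcome is labelled primary, and the unadjusted t-test that appears to lead is less precise than the baseline-adjusted regression already planned

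*Protocol article*

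**What the plan says.** The primary outcome is the 18-item Prostate Cancer Knowledge Scale, "administered at baseline and post-intervention surveys" (section 2.10.1). Section 2.12 gives two analyses of it:

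- The first: "We will assess pre-post intervention group differences on the Prostate Cancer Knowledge Scale using a two-sample" *t*-test. No covariates are named.
- The second: "Linear regression will also be used to estimate the post-intervention difference on the Prostate Cancer Knowledge Scale while accounting for" the baseline score and "demographic and psychosocial characteristics (e.g., age, insurance status" being the examples given.

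Neither carries the label primary, secondary or supportive. The two stratification factors of section 2.3, family history and reading level, are not named as covariates. Section 2.12 mentions them as expected to be balanced and as possible moderators.

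Elsewhere the contrast is worded differently. The abstract refers to "post-intervention group differences on the validated 18-item Prostate Cancer Knowledge Scale (primary outcome"), and the primary hypothesis in the Discussion is that men given the Genius App "will report significantly greater knowledge on the Prostate Cancer Knowledge Scale post-intervention than participants randomly assigned to the Taskforce App". The power statement (section 2.11) uses "a two-sided alpha of 0.05", 30 men per group, a baseline SD of 3.1 and a difference of 2.3 points. It uses no baseline-to-post correlation.

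**The concern.** A trial with one primary outcome should say which estimate and which p-value answer its hypothesis. Here the reader has to infer this from the order of sentences, from the word *also*, and from a power calculation that matches an unadjusted t-test. The term pre-post does not settle whether that t-test is on change scores or on post scores, and the abstract and hypothesis point to the latter.

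Precision is also at stake. Every participant completes the scale at baseline, and the plan already contains a model that uses that score. An unadjusted t-test on post scores ignores the baseline score. A t-test on change scores subtracts it with a fixed slope of 1, whereas regression estimates the slope from the data. With about 60 men analysed, the difference in power can be material.

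**Working it through.** **Inputs from the article.** 30 per arm, SD 3.1, difference 2.3, two-sided alpha 0.05, target power 80% (section 2.11).

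**Assumptions, not in the article.** The correlation ρ between baseline and post score is taken as 0.3, 0.5 or 0.7. The SD is taken as 3.1 at both times.

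**Step 1: reproduce the stated power.** The standard error of a difference in means is 3.1 × √(2/30) = 0.80, and the noncentrality is 2.3/0.80 = 2.87. The noncentral t with 58 df gives power 0.807 and a detectable difference of 2.28 at 80% power. The article's 80% for 2.3 points is reproduced. It fits a two-sample t-test on a score with SD 3.1.

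**Step 2: SD that enters each analysis.**

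- t-test on post scores: 3.1 at any ρ
- t-test on change scores: 3.1 × √(2(1−ρ)) = 3.67, 3.10, 2.40
- Regression adjusted for baseline (ANCOVA): 3.1 × √(1−ρ²) = 2.96, 2.68, 2.21

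**Step 3: variance relative to ANCOVA.**

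- Change scores: 2(1−ρ)/(1−ρ²) = 2/(1+ρ)
- Post scores: 1/(1−ρ²)

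**Step 4: power and detectable difference.** Noncentral t, with 58 df for the t-tests and 57 for ANCOVA.

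| | ρ = 0.3 | ρ = 0.5 | ρ = 0.7 |
|---|---|---|---|
| Variance ratio, change/ANCOVA | 1.54 | 1.33 | 1.18 |
| Variance ratio, post/ANCOVA | 1.10 | 1.33 | 1.96 |
| Power for 2.3, change t-test | 67% | 81% | 95% |
| Power for 2.3, post t-test | 81% | 81% | 81% |
| Power for 2.3, ANCOVA | 84% | 90% | 98% |
| Detectable at 80%, change | 2.70 | 2.28 | 1.77 |
| Detectable at 80%, post | 2.28 | 2.28 | 2.28 |
| Detectable at 80%, ANCOVA | 2.18 | 1.98 | 1.63 |

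At ρ = 0.4 the change-score t-test has 73% power. It reaches the stated 80% only if ρ is about 0.5 or higher, because at ρ = 0.5 the change SD equals 3.1.

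**Step 5: cost of the stratification terms.** Adding two terms to ANCOVA (55 df instead of 57), with no credit for any variance that they explain, lowers power by less than 0.1 percentage point at each ρ.

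**The case against.** The strongest reply is that the plan does imply a hierarchy. The t-test comes first, the regression is *also* used, and the power statement is that of an unadjusted t-test. The t-test is valid under randomisation, the adjusted regression is already planned, and the trial is a pilot of preliminary efficacy. Most of this stands. What is missing is an explicit label, and on this reading the analysis that leads is the less precise one.

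The size of the loss is conditional, as the reply would also say. It depends on ρ, which the article does not give, on equal SDs, and on how pre-post is read. If the t-test is on post scores, it meets the 80% target at every ρ.

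A reader might infer more than the text supports:

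- *That the two analyses address different effects.* They do not. Both use the same scale, and under randomisation both target the same mean difference in points. The estimates and p-values can differ, but the target does not.
- *That the plan allows a choice between the two results, with an inflated type I error.* In simulation, counting either the change-score test or ANCOVA as a success at 0.05 gives an error of about 0.078, 0.075 and 0.068 at ρ = 0.3, 0.5 and 0.7. The article does not propose such a choice, and its order suggests the opposite.
- *That covariates given by example invite selection by result.* A condensed article commonly leaves the final list to a fuller document, and nothing in the text suggests selection by result.
- *That the trial is underpowered.* This follows only on the change-score reading with ρ below about 0.5.

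**Conclusion.** The point holds as a should-fix. Section 2.12 does not label one analysis of the primary outcome as primary, and its wording of the contrast differs from that of the abstract and the hypothesis. The apparent lead analysis has a variance 18% to 54% larger than ANCOVA if it is on change scores, and 10% to 96% larger if it is on post scores, for assumed ρ from 0.3 to 0.7. Apart from one degree of freedom, ANCOVA is more precise than the change-score test at any ρ below 1, and more precise than the post-score test at any ρ that is not trivially small. So the direction of the result does not depend on the reading, but its size does. No stated figure is wrong and neither analysis is invalid.

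**What to change.** In section 2.12, name one primary analysis: linear regression of the post-intervention Prostate Cancer Knowledge Scale score on study condition, baseline score, family history and reading level. Report it as an adjusted mean difference with a 95% confidence interval. Label the two-sample t-test as supportive and say whether it is on change or post scores. Label any model with further demographic or psychosocial covariates as supportive too. Use the post-intervention wording in section 2.12, as the abstract and the hypothesis already do.

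The baseline score and both stratification factors are already collected, so no new data are needed. The cost is wording and a few degrees of freedom. The change should be made before outcomes are compared by group.
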